### Secondary outcomes

2.10

The use of the following scales was evaluated on the day of enrollment and the 20th day after treatment:

(1)insulin severity index;(2)Becker depression scale;(3)Becker anxiety scale.

The patients’ mood, sleep, and diet were followed up through the treatment log. All adverse reactions and causes of shedding will be recorded in case report form (CRF) in time.

### Estimation of sample size

2.11

The sample size was the minimum number of 30 cases in clinical trials. Considering the loss rate of 20%, 36 cases of N1 = N2 = 72 cases were selected in this study, and 36 cases of healthy controls were included.

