### Study design

2.1

This is a randomized, parallel controlled clinical trial. A total of 108 volunteers were recruited. Seventy-two patients with CI were randomly divided into 2 groups, the ratio was 1:1. Both groups were given basic treatment (sleep hygiene + cognitive therapy in CBT-I Technology), and the experimental group was added magnetic stimulation of HT7 points on the basis of basic treatment. There were 36 healthy people in the control group. There was no intervention in the healthy control group.

The whole study period was 20 days. The clinical efficacy was evaluated by clinical efficacy scale and related software on the day of enrollment and the 20th day of treatment.

The clinical trial results will be reported according to the Standards for Reporting

Interventions in Clinical Trials of Acupuncture statement.^[13]^

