### Statistical analysis

2.13

According to the situation of data collection, data analysis will be based on the principle of intention to treat analysis and / or per protocol analysis. We will also evaluate the group effect by comparing the analysis results of the above 2 data sets to evaluate the accuracy of our analysis results.

All data will be analyzed by third-party statisticians using SPSS 23.0 (v23.0, SPSS Inc, Chicago, IL). *P* < .05 was significant. Descriptive statistics will be carried out by group and time for average, standard deviation, maximum value, minimum value, and so on.

The data in accordance with the protocol set were selected for analysis. If the data obey normal distribution, they can be described by means, and standard deviation. If the variance is uniform, the analysis of variance of complete random design can be used to compare the effect indexes. If the variance is not uniform, the rank sum test of multi group comparison of complete random design can be used. If the data does not obey normal distribution, it can be described by median and interquartile distance. The hypothesis test used the bilateral test uniformly, with *P* < .05 as the statistical significance.

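### Section 2.11 allows for 20% loss by multiplying 30 by 1.2, so 36 per arm leaves an expected 28.8, slightly below the stated minimum of 30

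*Protocol article*

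**What the plan says.** Section 2.11 gives the whole basis for the trial's size in two sentences. The first sets the target: "The sample size was the minimum number of 30 cases in clinical trials". The second applies the loss allowance and gives the result: "Considering the loss rate of 20%, 36 cases of N1 = N2 = 72 cases were selected in this study". It adds 36 healthy controls. No formula, effect size, standard deviation or power is given.

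The figure of 72 is a total. Section 2.1 says: "Seventy-two patients with CI were randomly divided into 2 groups, the ratio was 1:1". Section 2.5 and the Abstract agree.

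Two other sections bear on whether losses reduce the analysed number. Section 2.3.5 withdraws patients who are lost to follow-up or who receive fewer than 30 stimulation sessions within 20 days, among other reasons. Section 2.13 names intention to treat and/or per protocol analysis, and then says: "The data in accordance with the protocol set were selected for analysis".

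**The concern.** The result of 36 is exactly what comes from adding 20% of the target to the target. That is not the allowance a 20% loss rate calls for. The loss falls on everyone enrolled, including the extra patients, so the target has to be divided by the retained fraction.

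The target of 30 is the only justification section 2.11 offers for the trial's size. If 36 per arm does not keep 30 at the stated loss, the plan misses its single size criterion on its own inputs, and a reader who takes the paragraph at face value will expect slightly more evaluable patients than the design provides.

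**Working it through.** **Inputs, all from section 2.11**
- Minimum number: 30. The text does not say per arm, but no other reading leads to 36 per arm.
- Loss rate: 20%.
- Enrolled: 36 per arm, 72 in total, allocated 1:1 (section 2.1).

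**Reproducing the plan's figure**
- 30 × (1 + 0.20) = 30 × 1.2 = 36. This matches exactly. The article shows no formula, so the multiplication is inferred, but it is the only standard step that gives 36.

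**What 36 per arm delivers at 20% loss**
- Per arm: 36 × (1 − 0.20) = 28.8, which is 30 − 28.8 = 1.2 short.
- Both arms: 72 × 0.8 = 57.6, against 60.

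**What keeping 30 would need**
- 30 / (1 − 0.20) = 37.5, rounded up to 38 per arm, or 76 patients.
- Expected completers: 38 × 0.8 = 30.4 per arm.
- The gap to the plan is 2 patients per arm, 4 in total.

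**Largest loss at which 36 still keeps 30**
- 1 − 30/36 = 6/36 = 16.7%.

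**Chance of retaining at least 30**

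This assumes that each patient is lost independently with probability 0.20, so the number retained is binomial with probability 0.80. The figure for both arms is the square of the figure for one arm.

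| Enrolled per arm | Expected retained | At least 30 in one arm | At least 30 in both arms |
|---|---|---|---|
| 36 | 28.8 | 0.401 | 0.401² = 0.161 |
| 38 | 30.4 | 0.655 | 0.655² = 0.43 |

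The second row is needed to read the first. Dividing by 0.8 protects the expected number and does not guarantee 30 in every arm. Much of the chance of falling short is binomial variation that would remain with 38; the inflation step accounts for the difference between the rows.

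**Do losses reduce the analysed number?** For the per protocol set, yes: patients withdrawn under section 2.3.5 leave it. Sections 2.9 and 2.10 measure outcomes only at enrolment and at day 20, so a patient lost before day 20 has no post-treatment value.

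**The case against.** The strongest case on the other side is that little depends on this. The shortfall is 1.2 expected completers per arm. It is measured against a conventional minimum, not a powered requirement, and the Discussion already calls the study a pilot and admits possible problems with sample size. This stands, and it limits the weight of the point.

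The 20% could also mean 20% of the 30, that is 6 patients, in which case 36 is enough. That is not the usual meaning of a loss rate. If it was intended, the loss among enrolled patients is 6/36 = 16.7%, and the paragraph still needs to say so.

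Section 2.13 also allows intention to treat. The shortfall is clear for the per protocol set. For an intention-to-treat set it depends on how missing day-20 values are handled, which the article does not show.

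Three stronger readings are tempting and are not supported:
- *The trial loses power it claims to have.* Section 2.11 claims none. It gives no effect size, standard deviation or power, so the shortfall cannot be turned into a loss of stated power.
- *The trial can be described as detecting about 0.75 SD with 80% power.* That value comes from an unadjusted t test on one outcome with 29 per arm. Section 2.9 lists three primary outcomes and section 2.13.1 plans rank sum or Chi-squared tests. With 29 per arm, the figure would be about 0.77 SD for a rank sum test on normal data and about 0.87 SD with a Bonferroni split over three outcomes.
- *Section 2.11 puts 72 patients in each arm.* Its equation can be read that way, but the same sentence gives 36, and sections 2.1 and 2.5 make 72 the total. This is loose wording only.

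**Conclusion.** The point holds as an arithmetic slip with a small consequence. At its own 20% loss rate, the plan's 36 per arm leaves an expected 28.8, below its own minimum of 30; the minimum would need 38 per arm. The conclusion rests on reading the 30 as per arm and the 20% as a share of enrolled patients. The probabilities also assume independent losses at the same rate in both arms.

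It does not show that the trial is underpowered, since nothing in the document fixes the power. That 30 has no stated statistical basis is the larger weakness of section 2.11, and correcting the inflation does not repair it. The paragraph should still be corrected, because the figure is wrong on its own terms and the correction is cheap.

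**What to change.** Keep 72 patients and restate section 2.11 along these lines: N1 = N2 = 36 (72 in total); at 20% loss about 29 patients per arm are expected to be evaluable; 30 per arm is reached only if loss is at most 16.7%. This also removes the ambiguous equation.

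Do not add a detectable-effect or power statement: the article gives no basis for one, and the unadjusted t test figure does not match the planned tests.

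If the sponsor prefers to hold 30 as the expected number, the alternative is 38 per arm (76 patients), with the repeated figures in the Abstract and sections 2.1, 2.5 and 2.12 changed to match.

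The recommended change costs one corrected paragraph, with no change to recruitment or design. The downside is that the stated evaluable number becomes slightly less favourable.

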### Randomization

2.12

This study is a randomized controlled open trial. The method of randomization and allocation concealment is to generate 72 serial numbers according to the order of visit. The first group was randomly assigned to the first group, and the second group was randomly assigned to the last group. The randomized grouping scheme was kept in a sealed envelope, and the envelopes were opened in turn according to the order of admission, and the grouping of patients was determined according to the allocation scheme in the envelope.

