#### Control group

2.7.2

The control group was only given basic treatment.

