### Primary outcomes

2.9

The cognitive function of the patients was evaluated on the day of enrollment and the 20th day after treatment:

1.1-back working memory;2.Rey osterieth complex figure test;3.Hanoi tower test.

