### Quality control

2.15

During the whole treatment and follow-up process, patients’ withdrawal and the reasons for withdrawal will be recorded in time. In order to ensure the test quality, the quality supervisor will regularly check all process details and check the authenticity of the data. In addition, the scientific research department of Shaanxi Provincial Hospital of traditional Chinese medicine will be invited to manage the data independently.

As differences between doctors may lead to errors, each evaluation of the scale will be performed by a designated physician trained in the same evaluation criteria. The 2 doctors in charge of the treatment will receive special training on research and operation, including the use of RMS and acupoint positioning. In order to record the patient's treatment and compliance, we made a record card for the patient, including the treatment date, personal information and signature after each treatment.

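### The trial is open with no sham, and nothing keeps whoever administers or scores the primary cognitive tests unaware of allocation; the Rey complex figure is the most exposed

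*Protocol article*

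**What the plan says.** Section 2.12 of the protocol article sets the masking status of the trial: "This study is a randomized controlled open trial". It adds no qualification for assessors.

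Section 2.7.2 describes the comparator: "The control group was only given basic treatment". There is no sham stimulation, so patients and treating doctors know who receives magnetic stimulation.

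Section 2.9 lists three primary outcomes: "1.1-back working memory;2.Rey osterieth complex figure test;3.Hanoi tower test". Section 2.1 describes how efficacy is measured: "The clinical efficacy was evaluated by clinical efficacy scale and related software". It does not say which test uses which mode.

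Section 2.15 says that "each evaluation of the scale will be performed by a designated physician trained in the same evaluation criteria". The reason given is that differences between doctors may cause error. A separate sentence says that "The 2 doctors in charge of the treatment will receive special training on research and operation". The section does not say whether these are different people.

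The independent functions that the plan does provide are statistical analysis (2.13: "All data will be analyzed by third-party statisticians using SPSS 23.0") and data management by the hospital's research department (2.15).

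**The concern.** Without a sham, patients and treating doctors cannot be masked. The person who runs and scores the tests can be, and masking that person is the main remaining guard against bias in how the cognitive outcomes are measured. The plan does not provide it.

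Training assessors to one standard reduces noise between raters. It does nothing about a shared or individual tendency to score one arm more generously, because that tendency comes from knowing the arm.

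Scoring a hand-drawn complex figure involves judgment about accuracy and placement. An assessor who knows the group can lean without intending to. Where a test is scored by software the score itself is safe, but instructions, encouragement and prompting during the session are not. The Discussion also declares an expected direction, since the authors say that they intend to confirm the benefit of the stimulation.

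What is at stake is whether a positive day-20 difference, above all on the complex figure, can be credited to the treatment rather than to the measurement.

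**Working it through.** **Step 1. Look for any protection of outcome measurement.**

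| Place in the protocol article | What it provides | Does it keep the assessor unaware of group? |
|---|---|---|
| 2.12 Randomization | Open trial; sealed envelopes | No; envelopes conceal allocation only until assignment |
| 2.7.2 Control group | Basic treatment only, no sham | No |
| 2.15 Quality control, assessment | Designated, uniformly trained physician | No; the stated purpose is consistency |
| 2.15 Quality control, treatment | Two trained treating doctors | No; separation from the assessor is not stated |
| 2.13 Statistical analysis | Third-party statisticians | No; they act after scores exist |
| 2.15 Quality control, data | Independent data management | No; it acts after scores exist |

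No section codes the test sheets or asks patients not to disclose their group.

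**Step 2. Ask which primary outcomes are exposed.**

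- Rey complex figure: a drawing whose scoring needs judgment. Both scoring and administration are exposed.
- 1-back: plausibly run on the software mentioned in 2.1. If so, only administration is exposed.
- Hanoi tower: the document does not give the mode. If run by software, it is as for the 1-back; if scored by hand, scoring is exposed too.

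Section 2.15 refers only to evaluations of the scale, and 2.10 uses the word scales for the secondary outcomes. It is therefore not settled that the designated physician handles the primary tests at all.

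**Step 3. Illustrate the size.** No figure in the plan depends on masking, so there is no stated result to correct. The inputs are:

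- Patients per arm: 36 (2.11). The plan's own route reproduces: 30 × 1.2 = 36.
- Patients per arm after loss: 30, the base figure in 2.11. As a check, 36 × 0.8 = 28.8, close to 30.
- Test level: two-sided 0.05 (2.13: "The hypothesis test used the bilateral test uniformly, with *P* < .05 as the statistical significance").
- Between-arm lean b, in SD units: **assumed**; the document gives none.

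The standard error of a standardised difference is SE = sqrt(2/n):

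- n = 36: sqrt(2/36) = 0.236
- n = 30: sqrt(2/30) = 0.258

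With no true effect, the probability of a significant result is Φ(b/SE − 1.96) + Φ(−b/SE − 1.96).

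| Assumed lean b (SD) | 36 per arm | 30 per arm |
|---|---|---|
| 0 | 5.0% | 5.0% |
| 0.1 | 7.1% | 6.7% |
| 0.2 | 13.6% | 12.1% |
| 0.3 | 24.7% | 21.3% |

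Worked line for b = 0.2 and n = 36: b/SE = 0.2/0.236 = 0.85, so Φ(−1.11) + Φ(−2.81) ≈ 0.133 + 0.002 ≈ 0.136.

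This is a normal approximation. Section 2.13.1 names rank sum or chi-squared tests for these outcomes, so the figures show scale and are not exact error rates for the planned analysis. They apply to one outcome at a time.

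**The case against.** **The word open does not prove that the assessor is unmasked.** The article is condensed, and silence about a safeguard is not a decision against it. This stands in part: the plan does not contradict itself here. But masking is a basic design feature, the article declares its status without qualification, and it does describe its assessor arrangements in 2.15. Anyone following the text as written would have no reason to mask the assessor.

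**A reader might infer that all three primary outcomes are scored by a rater.** The document does not support that. Section 2.1 mentions software, and 2.15 covers only scale evaluations. Scoring judgment is clear only for the complex figure. This objection stands and limits the point.

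**A reader might infer that an assessor separate from the treating doctors already exists, so masking costs nothing.** Section 2.15 mentions the two roles in different sentences, which suggests separation but does not state it. Nor does it say that there is only one assessor. The separation has to be written in, not assumed.

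**The illustrated error rates have no empirical basis in the document.** This is correct. The leans are assumptions, and at 0.1 SD the effect is small. A scoring lean does not arise for tests scored by software.

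**Masking the assessor leaves patients unmasked.** This is also correct. Expectation and effort can affect performance tests, and assessor masking does not remove that.

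**Conclusion.** The point holds in a limited form. The trial is open, the comparator has no sham, and nothing in the protocol article keeps whoever administers or scores the primary tests unaware of group. The arrangement in 2.15 deals with consistency only, and the independent analysis and data management come too late to protect the scores. The risk is clearest for the Rey complex figure. For the 1-back, and possibly the Hanoi tower, it may be confined to administration and prompting.

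The size is unknown. With an assumed lean of 0.1 to 0.3 SD on an affected outcome, the false-positive rate would be about 7% to 25% at 36 per arm, or about 7% to 21% at 30 per arm, instead of 5%. The document does not support saying that the trial has such an error rate, only that it leaves the route to one open. This is a correctable weakness that bears on the credibility of a primary outcome. It does not invalidate the design.

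**What to change.** Amend sections 2.12 and 2.15 to state that:

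- patients and treating doctors are open, but the outcome assessor is masked;
- the designated physician assesses all outcomes, including the three primary tests, and takes no part in treatment or allocation;
- that physician has no access to the envelopes, treatment logs or record cards;
- complex-figure drawings are scored under a code, without arm or visit label;
- where software runs a test, its score is taken directly, and the plan says which tests these are;
- patients are asked not to reveal their group to the assessor.

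Acknowledge as a limitation that bias from unmasked patients' own expectation and effort remains.

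The cost is a few sentences of protocol text and the coding of drawing sheets. If the assessor and the treating doctors are already different people, no further staff are needed. If they overlap, the roles must be separated, and that is a real cost. Some accidental unmasking by patients will still occur. The sample size and the analysis do not change.

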### Statistical analysis

2.13

According to the situation of data collection, data analysis will be based on the principle of intention to treat analysis and / or per protocol analysis. We will also evaluate the group effect by comparing the analysis results of the above 2 data sets to evaluate the accuracy of our analysis results.

All data will be analyzed by third-party statisticians using SPSS 23.0 (v23.0, SPSS Inc, Chicago, IL). *P* < .05 was significant. Descriptive statistics will be carried out by group and time for average, standard deviation, maximum value, minimum value, and so on.

The data in accordance with the protocol set were selected for analysis. If the data obey normal distribution, they can be described by means, and standard deviation. If the variance is uniform, the analysis of variance of complete random design can be used to compare the effect indexes. If the variance is not uniform, the rank sum test of multi group comparison of complete random design can be used. If the data does not obey normal distribution, it can be described by median and interquartile distance. The hypothesis test used the bilateral test uniformly, with *P* < .05 as the statistical significance.

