#### Withdrawal criteria

2.3.5

1.Violation of inclusion criteria and clinical trial protocol or exclusion criteria;2.Less than 30 sessions of RMS treatment were performed within 20 days;3.Serious adverse events occurred;4.Lost follow-up;5.Withdrawal of consent by subject or legal representative;6.Increase the treatment that may affect the study without the permission of the investigator.

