### Adverse events observation

2.8

Local skin numbness around HT7 point may be related to rMS of HT7 point. During the study, a patient treatment log will be established to monitor all adverse reactions during treatment and follow-up, and appropriate intervention will be carried out.

Patients with severe insomnia during the study were given dexzopiclone (3 mg QN). However, subjects who could not tolerate 80% of the rMS intensity and / or took more than twice a week of dexzopiclone were considered withdrawn.

In case of serious adverse reactions during the treatment, report to the principal investigator immediately, record the details in the patient treatment log and take corresponding treatment measures. If the subject or researcher thinks that the patient cannot tolerate these adverse reactions, the trial can be terminated and the subject will withdraw from the study.

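### Agreement between the ITT and per-protocol results cannot show that the result is accurate, because both can carry the same bias from missing day-20 scores

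*Protocol article*

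**What the plan says.** Section 2.13 (Statistical analysis) opens by saying that "data analysis will be based on the principle of intention to treat analysis and / or per protocol analysis". It then proposes "comparing the analysis results of the above 2 data sets to evaluate the accuracy of our analysis results". Two paragraphs later, before describing the tests, it states: "The data in accordance with the protocol set were selected for analysis". The article gives no criterion for agreement between the two results. It does not define the ITT set, and it does not say how a missing score is handled.

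Other sections bear on how the two sets could differ:

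- **Timing of outcomes (2.9):** "The cognitive function of the patients was evaluated on the day of enrollment and the 20th day after treatment". There is one post-baseline score and no interim one.
- **Withdrawal (2.3.5):** the reasons include "Less than 30 sessions of RMS treatment were performed within 20 days" and "Lost follow-up".
- **Adverse events (2.8):** "subjects who could not tolerate 80% of the rMS intensity and / or took more than twice a week of dexzopiclone were considered withdrawn".
- **Sample size (2.11):** the plan allows for a 20% loss and randomises 36 per arm.
- **Randomization (2.12):** the trial is open.

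**The concern.** The article gives the comparison a purpose that it cannot serve. The ITT and per-protocol sets overlap heavily. When they agree, the patients who separate them made little difference. That says nothing about patients who are in neither.

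Several features make this more than a formality here. With a single post-baseline assessment, a lost patient leaves no partial outcome. Patients and treating staff know the allocation. Two withdrawal rules, incomplete rMS sessions and intolerance of the rMS intensity, can apply only to the stimulation arm. Withdrawal for repeated rescue use is plausibly related to sleep and cognition. If loss in the stimulation arm is related to a poor result, both estimates move in favour of stimulation. The trial could then report that its accuracy had been checked when the check could not see that error.

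**Working it through.** **The plan's own figure.** Section 2.11 starts from 30 per group and a 20% loss. 30 × 1.2 = 36 per arm, or 72 randomised, which matches the text. (Dividing instead, 30 / 0.8 = 37.5, gives 38; the present point does not depend on this.) A 20% loss from 36 is 7.2, so I take 7 withdrawn and 29 remaining per arm.

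**Assumptions, none of them from the documents.** The true effect is 0 and the outcome SD is 1. Control withdrawal is random. Withdrawal in the stimulation arm takes the 7 patients lowest on a variable that correlates *r* with the day-20 score. A share *f* of withdrawn patients is nevertheless scored. ITT means all patients with a score, without imputation; per protocol means the patients not withdrawn.

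**Closed form (large-sample normal approximation).** The withdrawn fraction is p = 7/36 = 0.194. The normal cut-point is −0.862, with density 0.275.

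- Mean of the withdrawal variable among those kept: 0.275 / 0.806 = 0.342.
- Mean among those withdrawn: −0.275 / 0.194 = −1.415.
- Per-protocol bias = r × 0.342.
- ITT bias = r × (29 × 0.342 − 7f × 1.415) / (29 + 7f).

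At f = 0 the ITT formula reduces to the per-protocol one, because the two sets are the same patients. At f = 0.5 the factor is (9.91 − 4.95) / 32.5 = 0.152. At f = 1 it is 0.

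**Simulation of the same set-up** (4,000 trials per cell; biases in SD):

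| r | Per-protocol bias | ITT bias, f = 0 | ITT bias, f = 0.5 | ITT bias, f = 1 |
|---|---|---|---|---|
| 0 | 0 | 0 | 0 | 0 |
| 0.3 | 0.10 | 0.10 | 0.04 | 0 |
| 0.5 | 0.17 | 0.17 | 0.08 | 0 |
| 0.8 | 0.27 | 0.27 | 0.12 | 0 |

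The closed form gives 0.10, 0.17 and 0.27 for per protocol, and 0.05, 0.08 and 0.12 for ITT at f = 0.5. The two agree within 0.01 SD.

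The gap between the estimates is therefore exactly 0 when no withdrawn patient is scored, although both are biased. It is about 0.06, 0.09 and 0.15 SD when half are scored. When all are scored it equals the whole per-protocol bias, and the comparison then works as intended.

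**A second loss model.** Here the log-odds of loss in the stimulation arm are −1.7 − 1.0 × score in SD, about 20% lost. Control losses are 20% at random, and a further 0, 5, 10 or 20% is removed at random from the per-protocol set. The scores of lost patients are not used.

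- Bias in both sets: about 0.16 to 0.17 SD.
- Correlation of the two estimates: 1.00, 0.97, 0.95 and 0.89.
- Same significance verdict: 100, 97.3, 95.2 and 93.8% of trials.
- False-positive rate: 9.2 to 10.1% against a nominal 5%.

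These runs used a t-test, whereas sections 2.13.1 and 2.13.2 name rank sum or chi-squared tests. With half of the withdrawn patients scored, this model gives an ITT bias of 0.08 SD against 0.17 SD per protocol.

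**The case against.** The strongest reply is that withdrawn does not mean unscored. A patient with too few sessions, or counted as withdrawn for intolerance or rescue use, may still be assessed at day 20. That patient would be in the ITT set and outside the per-protocol set, which is the contrast such a comparison is meant to examine. Of the listed reasons, only loss to follow-up directly implies a missing score; withdrawal of consent may do so. The ITT analysis might also impute missing scores, and a condensed article may leave that to an analysis plan that is not shown.

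This stands, and it limits the point. A reader might infer that all withdrawn patients are absent from both sets, that the check is bound to pass, or that the trial has no other robustness check. The article supports none of these. It is silent on scoring after withdrawal and on imputation, it sets no pass criterion, and the full plan is not at hand.

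It is also fair to say that the second loss model partly builds in its own agreement. Random further removal cannot separate the two estimates on average, and much of the shared verdict is two non-significant tests. The common bias is the better evidence, and it rests on an assumed link between loss and outcome.

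Finally, accuracy may be loose English for robustness, and the Discussion calls the study a pilot. Even on that reading, agreement is not evidence about patients whom neither analysis takes into account.

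**Conclusion.** The point holds in a limited form. The article states a use of the ITT and per-protocol comparison that does not follow, so this is a stated rule fixed badly and not a missing detail. Agreement cannot establish accuracy with respect to any randomised patient who lacks a day-20 score and is not otherwise accounted for in the ITT analysis.

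At the planned 20% loss, with loss related to outcome in the stimulation arm only, the undetected common bias is about 0.17 SD at a moderate association (0.10 to 0.27 SD for r from 0.3 to 0.8). The comparison becomes partly informative as more withdrawn patients are scored, and the bias vanishes if all are scored or if loss is unrelated to outcome. None of this shows that the trial's result will be biased; it shows that the proposed check could not rule that out.

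The choice between the two sets is a related weakness. The opening sentence allows either or both, and a later one selects per protocol, so the comparison may not be made at all. Naming one set as primary would still leave the accuracy statement unsound. The defect should be corrected, but it overstates how well the result has been checked and does not invalidate the design.

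**What to change.** In section 2.13:

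1. Delete the statement that comparing the two sets evaluates accuracy.
2. State that all 72 randomised patients are analysed by assigned group, using the day-20 score of a withdrawn patient wherever one was obtained.
3. Report the per-protocol analysis as supplementary only, and change the sentence that selects the protocol set accordingly.
4. Add a delta-adjusted (tipping-point) analysis. Impute missing day-20 scores, worsen the imputed values in the stimulation arm step by step until significance is lost, and state whether the conclusion survives plausible shifts.

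Do not make the test depend on giving missing stimulation patients the worst rank and missing controls a middle rank. With 7 of 36 missing at random per arm and a true effect of 0.8 SD, simulation puts favourable significance at about 81 to 83% for the observed-case rank sum test and 9% under that scoring. With no effect, it declares stimulation significantly worse in 26% of trials.

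The cost is a few changed sentences and one further analysis of existing data. The downside is that a positive result may look less robust.
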